### Participants

Patients aged between 18 and 60 years are recruited from four Dutch tertiary clinics specialized in the treatment of anxiety and eating disorders. Patients diagnosed with AN (both restrictive and binge/purge subtype) are recruited from Altrecht Eating Disorders Rintveld, Zeist, and Rivierduinen Eating Disorders Ursula, Leiden, and patients with OCD from Altrecht Academic Anxiety Centre, Utrecht, and Overwaal Centre for Anxiety Disorders, Nijmegen. Most of the patients referred to these centres suffer from moderate to severe AN or OCD.

Eligible are patients whose AN (or eating disorder not otherwise specified, clinically referred to as AN) or OCD diagnosis is consistent with the Diagnostic and Statistical Manual of Mental Disorders, fourth edition text revision (DSM-IV-TR ).

The criteria for exclusion are: severe neurological illness (including a history of seizures, stroke, or Parkinson’s disease), severe comorbid psychiatric disorder (clinical significant major depressive disorder, current acute phase of bipolar disorder, current psychosis, substance dependence/abuse), intellectual impairment, defined as an IQ < 80, estimated with the Dutch Adult Reading Test (DART) [61], which is a Dutch version of the National Adult Reading Test (NART) [62], and inability to adequately speak or read Dutch. Current use of antidepressants and antipsychotics is allowed provided that dosages are kept constant during the experimental part of the study. Since benzodiazepines can dampen the effect of cognitive treatments [63], their use is restricted to a daily maximum dose (up to 20 mg for temazepam or an equivalent dose) taken as a sleep medication. On request, patients can withdraw their participation at any time.

Inclusion and exclusion criteria are verified with the aid of the structured clinical interview for DSM-IV-TR axis I disorders (SCID-I [64]), while for OCD patients to be enrolled, a Yale-Brown Obsessive-Compulsive Severity Scale score ≥16 is required [65, 66]. In all patients comorbidity with either OCD or AN is allowed.

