### Procedure and randomization

All participating centres adhere to standardized intake and screening procedures. The therapist performing the screening informs patients meeting the inclusion criteria about the study and ask their permission to have a research assistant contact them by phone or in person to invite them to participate in the trial, after which interested patients are sent or given a brochure describing the study. At least 1 week later baseline assessments are carried out after written informed consent is obtained. After baseline assessments patients not meeting inclusion-criteria are excluded. Patients satisfying all the study criteria are subsequently randomized to one of the two study conditions. An independent research coordinator who is not involved in the therapies or assessments uses SPSS/IBM [67] to create a randomization sequence stratified by treatment centre with a 1:1 allocation using random block sizes of 4. Given the nature of the study design, all patients and therapists are aware of the treatment condition (CRT or SAT). Patients are informed that both treatment arms are being investigated as to their potential to enhance subsequent TAU. The therapists delivering CRT or SAT are instructed not to reveal the treatment condition to the research assistant conducting the assessments; unintended violation of assessor blindness is recorded.

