### Power and sample-size calculation

In accordance with Cohen [117], we calculated the sample sizes needed to detect treatment-specific differences: CRT + TAU vs. SAT + TAU, for which we used software by G-power [118].

We based effect-size calculations on Dingemans’ first RCT [57] comparing CRT + TAU with TAU alone for eating disorders in which they obtained large effect sizes for reduction in eating disorder pathology (Cohen’s d: 0.99). Given the control condition in this study we take into account a smaller effect-size. In the case of two-tailed MANOVAs, repeated measures and four within-between interactions (2 groups: AN and OCD), two conditions (CRT + TAU vs. SAT + TAU), three measurements (baseline, and 2, and 6 months after baseline), with alpha = 0.05, a sample size of 113 patients is needed to have a power of at least 0.80 to detect an effect size f(V) of 0.25. Although the dropout rate in the previous CRT studies of Dingemans was low (*n* = 7 out of 82 patients), we have opted to include an additional 15 patients to compensate for attrition, totalling 128 patients in total (64 CRT + TAU and 64 SAT + TAU).

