### Treatment as usual

After completion of either CRT or SAT, patients receive TAU. The content of TAU comprises all the essential elements recommended in the Dutch guidelines on eating disorders and OCD, which are closely related to the international guidelines [121, 122].

TAU for patients with AN consists of normalization of eating behaviours (weight gain), discussion of daily problems, goals, psycho-education, and for a subgroup psychomotor therapy, art therapy, social skills training, family-therapy or cognitive behavioural therapy. Psychiatric- and/or medical consultation and pharmacotherapy is given where needed.

TAU for OCD patients comprises CBT delivered in 20 to 30 weekly or twice weekly 45–90 min sessions in which exposure with response prevention forms a key element, consistent with the multidisciplinary guidelines for anxiety disorders (OCD chapter) [121]. In line with the literature [123, 124], the OCD protocol is flexible, i.e., patient-tailored with regard to the time spent on each component, accounting for differences in session and treatment duration. The therapy encompasses a) psychoeducation, b) cognitive therapy, c) exposure in vivo with response prevention, d) psychiatric consultation, and, in case of severe symptoms, pharmacotherapy with SSRIs, venlafaxine, clomipramine and/or atypical antipsychotics. The protocol allows for one or two sessions in which the principles of CBT are explained and one or two sessions in which an inventory is made of all anxiety/tension-provoking situations that give rise to compulsions and a construction of a list of compulsion triggers. All patients receive in- and between session exposure to anxiety-provoking thoughts and situations, coupled with prolonged response prevention tailored to their individual symptoms.

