### Analyses

Baseline differences between the CRT and SAT (control) groups and between the participating centres are investigated using χ^2^ tests for categorical variables and ANOVAs for continuous variables. Additional exploratory analyses are conducted separately for AN and OCD.

The data for the primary AN and OCD outcome indices are analysed using linear mixed models (LMM) with the baseline value as a covariate. The mixed models analysing the general efficacy of CRT include a random term for the intercept and fixed terms for condition, time contrasts (T0–T1, T0–T2, T0–T3, T1–T2, T1–T3), and the interactions between condition and time contrasts.

In order to investigate moderators of short- and long-term treatment response, time contrasts are created (T0–T1, T0–T2, T0–T3, T1–T2, T1–T3) by means of dummy coding. Potential continuous moderator variables are standardized. Interactions between condition and the potential moderators are entered into the equation. All analyses on therapy effect modificators are of an exploratory nature. The moderator and mediator analyses are calculated with 5000 bootstraps [126].

To assess the cost-effectiveness of CRT + TAU versus SAT + TAU for ED and OCD, all relevant costs and effects are taken into account. Disease progression is described in terms of transitions between ‘states’, where a patient’s ‘state’ can shift in either direction or remain constant. Estimations of state-transition rates are based on the data from the ongoing trial and the literature, which modelling approach serves to help us assess future scenarios. Costs and effects are calculated in accordance with recommendations in the Dutch guideline for economic evaluation of health care. As a primary assessment we apply a costs-utility analysis that yields a cost per quality-adjusted life years (QALY) outcome, a common cost-effectiveness measure that allows comparison with economic evaluations of other diseases and interventions. The uncertainty estimations are computed using bootstrapping and the results expressed in an acceptability curve. If no intervention is effective, a cost-minimization calculation is performed.

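### Randomisation is stratified by centre, but the primary mixed model as listed has no centre term, which makes the test of between-patient condition effects somewhat conservative

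*Protocol article*

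**What the plan says.** Under Procedure and randomization, the coordinator is to "create a randomization sequence stratified by treatment centre with a 1:1 allocation using random block sizes of 4". Under Participants, patients are "recruited from four Dutch tertiary clinics specialized in the treatment of anxiety and eating disorders". Two of the clinics supply the AN patients; the same sentence takes "patients with OCD from Altrecht Academic Anxiety Centre, Utrecht, and Overwaal Centre for Anxiety Disorders, Nijmegen". Each centre therefore recruits for one disorder, and knowing the centre means knowing the disorder.

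Under Analyses, the primary outcomes go into "linear mixed models (LMM) with the baseline value as a covariate". The terms follow: "The mixed models analysing the general efficacy of CRT include a random term for the intercept and fixed terms for condition, time contrasts", with five time contrasts over T0 to T3 and their interactions with condition. Centre appears in that section once, in the comparison of baseline characteristics. Separate analyses by disorder are described there as supplementary and exploratory.

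The power section counts two disorders, two conditions and three measurements. It arrives at 113 patients, raised to 128 for attrition.

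**The concern.** Blocked allocation within centre keeps the arms balanced in each centre, so differences in outcome level between centres cannot contribute to the treatment difference. A model without centre still counts those differences as residual variation. The reported standard error then describes a less precise trial than the one that was run. Confidence intervals come out too wide, the test rejects less often than its nominal level, and some power is lost.

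The stake is efficiency in a trial of modest size. It is also good to settle the matter before unblinding, because otherwise a choice between centre-adjusted and unadjusted results could be made after both are seen.

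**Working it through.** **Inputs.** Four centres, two per disorder (Participants). Stratification by centre, 1:1 (Procedure and randomization). Two-sided alpha 0.05, power 0.80, f(V) = 0.25, N = 113 before and 128 after the attrition allowance (Power and sample-size calculation). Model terms (Analyses). The share ρ of baseline-adjusted outcome variance lying between centres is **assumed**, since the document gives no figure. The range used is 0.02 to 0.20.

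**Step 1: the plan's own figure.** Take a repeated-measures MANOVA, within-between interaction, with k = 4 groups (disorder by condition) and m = 3 measurements. Then p = m − 1 = 2 and s = min(p, k − 1) = 2.
- df1 = 2 × 3 = 6
- df2 = s(N − k − p + s) = 2 × (113 − 4 − 2 + 2) = 218
- λ = N·s·f(V)² = 113 × 2 × 0.0625 = 14.125

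Power is 0.803, so 113 is reproduced. With two groups instead of four, the required N would be 158. The power basis thus contains disorder as a factor. The present point does not change 113 or 128.

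**Step 2: standard error and actual alpha without centre.** With arms balanced within centre, the true variance of the treatment difference rests on the within-centre variance (1 − ρ)σ². A model without centre uses σ².
- Reported SE / true SE = 1/√(1 − ρ)
- Actual alpha = 2[1 − Φ(1.96/√(1 − ρ))]

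Neither expression depends on N, so both serve for a pooled model and for one fitted per disorder.

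**Step 3: power.** As an illustration, take a two-arm contrast that has 80% power at N = 113 when ρ = 0. In units of the total SD, d = (1.960 + 0.842) × 2/√113 = 2.802 × 0.188 = 0.53. At N = 128 the SE with ρ = 0 is 2/√128 = 0.177.
- Without centre: Φ[(0.527 − 1.96 × 0.177)/(0.177√(1 − ρ))]
- With centre: Φ[0.527/(0.177√(1 − ρ)) − 1.96]

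| Assumed ρ | SE overstated by | Actual alpha | Power without centre | Power with centre |
|---|---|---|---|---|
| 0.02 | 1.0% | 0.048 | 0.849 | 0.854 |
| 0.05 | 2.6% | 0.044 | 0.853 | 0.864 |
| 0.10 | 5.4% | 0.039 | 0.859 | 0.882 |
| 0.20 | 11.8% | 0.028 | 0.873 | 0.915 |

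**Step 4: check by simulation.** Four centres of 32 (equal sizes assumed), blocks of 4, baseline-adjusted comparison.
- ρ = 0.10: without centre, mean SE 0.177 against a true 0.168, type I error 0.039; with centre, SE 0.168 and type I error 0.050.
- ρ = 0.20: without centre, SE 0.177 against 0.161, type I error 0.030; with centre, SE 0.158 and type I error 0.053.

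**Step 5: condition by time contrasts.** A random-intercept mixed model (intercept read as patient-level) was fitted to T1 to T3 with ρ = 0.20, 150 replicates per scenario.
- Centre effect constant over follow-up: the SE of condition at T3 is 0.176 without centre (true 0.161) and 0.158 with it. The SE of condition by (T1–T3) is 0.157 either way.
- Centre effect growing from nothing at T1 to its full size at T3: the SE of condition by (T1–T3) is 0.168 without centre, 0.168 with a centre main effect, and 0.158 only with centre by time.

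A stable centre difference therefore cancels from within-patient contrasts. Only diverging courses cost precision there, and only centre by time addresses that.

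**Step 6: parameters added.** Per disorder with four visits: 1 for centre + 3 for centre by time = 4. Pooled: 3 + 9 = 12. If T0 enters only as a covariate, leaving three visits as outcomes, these become 1 + 2 = 3 and 3 + 6 = 9.

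**The case against.** **The list may not be complete.** The article says what the models include, and the baseline covariate stands in a separate sentence. A condensed article may leave stratification covariates to a fuller plan. This has some force. But the text goes down to the random term, the fixed terms and each time contrast, and its only use of centre is for baseline comparison. That is a stated model that does not match the stated allocation scheme.

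**The loss may be negligible, and it errs on the safe side.** This stands. Baseline adjustment already removes part of any centre difference in level, only the remainder counts, and its size is unknown. At ρ of 0.05 or less, power moves by about one percentage point or less.

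**The main contrasts may be untouched.** This also stands in part. The model is built around condition by time terms, and a stable centre effect cancels from within-patient contrasts (Step 5). The table must not be read across to them.

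**Courses differing by centre are not shown.** A reader might infer such differences from the description of usual treatment, where "the OCD protocol is flexible, i.e., patient-tailored with regard to the time spent on each component". That describes tailoring to patients, in OCD only. It does not say that centres differ, and the same section ties usual treatment to the national guidelines.

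**A disorder term may not be missing.** A reader might infer that it is. The four-group power calculation and the exploratory status of the by-disorder analyses point towards pooling. But the two disorders have different primary instruments, EDE-Q and Y-BOCS, which points towards one model per outcome, and there a disorder term is redundant. The text leaves this open, so the omission of disorder cannot be asserted outright.

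**Conclusion.** The primary model as listed omits the factor by which patients are randomised. For between-patient condition effects after baseline adjustment, the standard error is overstated by 1.0% to 11.8%, and the two-sided 5% test runs at 0.048 down to 0.028, for assumed centre shares of 2% to 20%. The effect is small up to about 5% and becomes material from about 10%. These figures rest on the assumed share and on near-exact balance within centre. For condition by time contrasts the loss is conditional on courses that differ between centres, on which the document is silent.

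Two stronger conclusions are tempting but unsupported. One is that the analysis is biased or anti-conservative: the error runs the other way. The other is that adjustment is worth a fixed gain in patients, such as 1/(1 − 0.20) = 1.25 times the sample. That figure depends wholly on an assumed 20% share and does not apply to within-patient contrasts when the centre effect is stable. The point is a worthwhile, low-cost improvement and does not threaten the validity of the trial.

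**What to change.** Add centre as a fixed effect to the primary and secondary mixed models, and add centre by time so that the change contrasts are covered as well as the condition effects at follow-up. A centre main effect alone would not help the change contrasts.

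Use two centre levels in a model fitted within one disorder and four in a pooled model, where centre already carries the disorder main effect. No separate disorder term is needed if models are fitted per outcome. State which of the two forms is primary.

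The cost is a line of specification and up to 4 parameters per disorder, or up to 12 in a pooled model with four visits. Sample size, data collection and trial conduct are unaffected.

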### Study aims

The primary goal of the current ongoing study is to examine the treatment enhancing effect of CRT on treatment as usual (TAU, guideline directed therapy) in AN and OCD. The secondary aim is to investigate the cost-effectiveness and budget impact of CRT. The third aim is to study which patient characteristics determine positive benefits from CRT-based treatment enhancement. More specifically, we study several moderators and mediators of response (Table 1).

**Table 1 Tab1:** Measures to assess screening, outcome, mediator and moderator variables

Function	Measure	Instrument	T0	T1	T2	T3
Screening	Diagnostic status	SCID	X			
Primary outcome	AN severity	EDE-Q	X	X	X	X
	OCD severity	Y-BOCS	X	X	X	X
Secondary outcome	OCD severity	OCI-R	X	X	X	X
	Quality of life	EQ-5D	X	X	X	X
		ED-Qol ^c^	X	X	X	X
		OCD-Qol ^b^	X	X	X	X
	Daily functioning	WSAS	X	X	X	X
	Healthcare utilization and production loss	TIC-P	X	X	X	X
	Depression	BDI-II	X	X	X	X
	General anxiety	BAI	X	X	X	X
Mediators	Cognitive flexibility	Stroop	X	X	X	X
		D-Flex	X	X	X	X
		TMT	X	X	X	X
	Response inhibition	SSRT	X	X	X	X
	Central coherence	GEFT	X	X	X	X
	Intolerance of uncertainty	IUS	X	X	X	X
	Perfectionism	CPQ	X	X	X	X
	Self-efficacy	PEPPI-5	X	X	X	X
	Behaviour inhibition/activation	BISBAS	X	X	X	X
	Therapeutic engagement	SRS ^a^	X			
Moderators	Demographics, e.g. sex, age, education level	Interview	X			
	Diagnostic status	SCID-I	X			
	Obsessive compulsive personality disorder	SCID-II-OCPD	X			
	Autism	AQ	X			
	ADHD	CAARS-S:SV ^b^	X			
	Cognitive flexibility	ID/EDS ^b^	X			
	Planning ability	BADS-Zoo-map	X			

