### Design

Figure 1 provides an overview of the study design. In a randomized controlled multicentre trial, we compare two treatment arms, i.e. CRT and, in the control condition, Specialized Attention Therapy (SAT), both delivered in 10 twice weekly sessions as an adjunct to TAU for AN and OCD. Patients are assessed at baseline (T0), directly following CRT or SAT completion and prior to symptom based TAU (T1), at 6 months after T0; (T2), and at 12 months after T0 (T3). All patients receive both oral and written information and are enrolled after they have provided written informed consent.

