### Measures

Table 1 provides a list of screening, outcome, mediator and moderator measures. Assessments to monitor treatment progress are performed at baseline (T0), after 2 months (post-CRT or SAT and prior to TAU) (T1), and 6 months after the baseline TAU (T2), and after 12 months (T3) This measurement will encompass the same instruments as used at T2. All patients are extensively re-evaluated using (validated or recommended) indices of treatment effect and costs, quality of life, and cognitive and behavioural flexibility, which will entail self-reports, structured clinical interviews, and paper-and-pen as well as computerized neuropsychological tests. All screening and outcome data are collected in a central database using SPSS/IBM [67].

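### The efficacy model lists five overlapping condition-by-time contrasts with none primary, one of them ends before TAU begins, and T2 is dated in two incompatible ways

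*Protocol article*

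**What the plan says.** All references are to the protocol article.

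- **Study aims.** The primary goal is to "examine the treatment enhancing effect of CRT on treatment as usual" in AN and OCD.
- **Outcome measures.** The primary scale is the EDE-Q for AN and the Y-BOCS for OCD. No time point is attached to either, and Table 1 schedules both at T0, T1, T2 and T3.
- **Analyses.** The primary indices go into linear mixed models with the baseline value as covariate. The fixed terms are condition, "time contrasts (T0–T1, T0–T2, T0–T3, T1–T2, T1–T3), and the interactions between condition and time contrasts". The same section describes separate AN and OCD analyses as additional and exploratory, in the paragraph on baseline comparisons.
- **Power and sample-size calculation.** The planned test is described as "In the case of two-tailed MANOVAs, repeated measures and four within-between interactions". It crosses the two disorders with the two arms and uses "three measurements (baseline, and 2, and 6 months after baseline". The result is: "with alpha = 0.05, a sample size of 113 patients is needed to have a power of at least 0.80".
- **Design.** Assessments fall "directly following CRT or SAT completion and prior to symptom based TAU (T1), at 6 months after T0; (T2". T3 comes one year from T0.
- **Measures.** T1 is placed at 2 months and before TAU, but T2 is "6 months after the baseline TAU (T2".

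**The concern.** A primary outcome is fixed only when scale, time point and comparison are all fixed. Here the scale is given, but the model offers five comparisons of equal standing, and a reader cannot tell which one decides whether CRT worked. One of them covers only the phase before TAU, although the aim is enhancement of TAU. The trial was sized for something else: a single interaction test that stops at 6 months. In addition, the 6-month assessment is the natural primary time point, because the sample-size calculation ends there, yet two sections date it differently. What is at stake is the freedom to choose the favourable time point after seeing the data, and a main result whose timing is not settled.

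**Working it through.** **1. The plan's own figure.** Inputs from the Power section: 4 cells (2 disorders × 2 conditions), m = 3 measurements, f(V) = 0.25, alpha 0.05, power at least 0.80. For the Pillai-trace test of the within-between interaction:

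- s = min(k − 1, m − 1) = min(3, 2) = 2
- df1 = (k − 1)(m − 1) = 3 × 2 = 6
- df2 = s(N − k − (m − 1) + s) = 2(113 − 4 − 2 + 2) = 218
- noncentrality = f(V)² × s × N = 0.0625 × 2 × 113 = 14.125

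Power is 0.803 at N = 113 and 0.799 at N = 112, so 113 is reproduced exactly, and 113 + 15 = 128. With four measurements the same formula gives N = 87, and with only two groups it gives 158. The stated size therefore belongs to one omnibus test on all four cells, ending at 6 months. T3 is not in it.

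**2. The five contrasts.** Write the four assessments as T0 to T3. Then

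- (T1–T2) = (T0–T2) − (T0–T1)
- (T1–T3) = (T0–T3) − (T0–T1)

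The 5 × 4 contrast matrix has rank 3. Two of the five terms are exact combinations of the others, and the same holds for their interactions with condition. The model as listed cannot be fitted with all five as fixed terms. T0 is also adjusted for as a covariate while being one end of three of the contrasts.

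**3. T0–T1 against the aim.** T1 is at the end of CRT or SAT and before TAU (Design, Measures). T0–T1 contains no TAU, so a difference there is an effect of CRT alone.

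**4. False-positive rate.** Assumptions, none of which the article states: each contrast is tested separately, two-sided at 0.05, without correction, and any one counts as success. Because the listed model is not estimable, each contrast was treated as its own normal test under no effect (1,000,000 draws).

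| Correlation over time | One analysis, f | Two disorders, 1 − (1 − f)² |
|---|---|---|
| Equal, r = 0.3 to 0.8 | 0.182 | 0.330–0.331 |
| Decaying over months 0/2/6/12 | 0.162–0.176 | 0.298–0.321 |
| Baseline-adjusted, r = 0.3 to 0.7 | 0.182–0.183 | 0.331–0.332 |

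For comparison, independent tests would give 1 − 0.95⁵ = 0.226 and 1 − 0.95¹⁰ = 0.401. Dropping only T0–T1 leaves 0.162 and 0.297 (equal correlation, r = 0.5), so that step alone does little.

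**5. T2.** The Design section puts T2 at month 6 from T0, and the Power section also counts 6 months from baseline. The Measures section counts 6 months from the baseline of TAU. If TAU starts at T1, month 2, that is 2 + 6 = month 8. The two datings are about 2 months apart.

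**The case against.** **Is it one in three?** A reader might infer a flat false-positive rate of about one in three. That needs AN and OCD to be two confirmatory families. The article does not say so: it calls the separate analyses exploratory and sizes one test on the combined sample. Nor does it settle the opposite, because the exploratory remark sits with the baseline comparisons, the primary scales differ by disorder, and no common scale is given. Both readings stay open, so only the range can be stated.

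**Would a significant T0–T1 be declared a success?** No success rule and no per-contrast alpha appear in the article. Listing a contrast as a model term does not make it decisive, and an early effect is legitimate to report. The objection stands; what remains is that nothing separates T0–T1 from the contrasts that bear on the aim.

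**Is the lack of a multiplicity rule a fault?** No. An analysis plan that is not shown may contain one, and an article commonly leaves it there. The point rests on the structure that the article does fix.

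**Does the T2 conflict mix mid-treatment and post-treatment scores?** A reader might infer this, but the cause would be different. TAU for OCD runs to 20 to 30 weekly or twice-weekly sessions, so any fixed date catches patients at different stages. The Measures phrase is also the outlier and may be a slip. It still contradicts the Design section.

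**Conclusion.** The point holds as a should-fix. Three parts are firm and need no assumption: no contrast is primary among five that have only rank 3, T0–T1 ends before the treatment it is meant to enhance, and the T2 datings conflict by about 2 months if TAU starts at T1. The mismatch with the sample size is also firm, since 113 is reproduced only as one interaction test on three measurements. The error rate is conditional: 0.16–0.18 for one pooled analysis or 0.30–0.33 for two confirmatory disorders, given uncorrected tests at 0.05 and any-one-wins. Both exceed three times the 0.05 used for sizing, but neither is a rate that the article commits itself to.

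**What to change.** 1. Name one primary contrast: the baseline-adjusted CRT–SAT difference at T2.
2. Count T2 from T0 throughout, as the Design and Power sections do, and reconcile the Measures section with them.
3. Label the other contrasts secondary, and report T1 as the effect before TAU. Code time with three independent contrasts, and use T0 either as covariate or as an outcome.
4. State whether the disorders are pooled (one test at 0.05, with the common scale named) or tested separately (Holm over two). One contrast tested at 0.05 in each disorder would give 1 − 0.95² = 0.0975; Holm holds this to at most 0.05.

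**Cost.** The edits are small, but other time points can no longer carry a confirmatory claim. If the disorders are tested separately, Holm also lowers power. As an illustration, assume d = 0.5 (not in the article; f(V) does not convert to it directly) with 32 per arm (64 per disorder, 1:1). The noncentrality is 0.5 × √16 = 2.0, and power falls from about 50% at 0.05 to 39% at the first Holm step of 0.025. With baseline adjustment at an assumed correlation of 0.5, noncentrality is 2.0/√0.75 = 2.31, and power falls from about 62% to 51%.
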